## Abstract

**Background:**

Postoperative complications and readmissions to hospital are factors known to negatively influence the short- and long-term quality of life of patients with gastrointestinal cancer. Active family involvement in activities, such as fundamental care activities, has the potential to improve the quality of health care. However, there is a lack of evidence regarding the relationship between active family involvement and outcomes in patients with gastrointestinal cancer after surgery.

**Objective:**

This protocol aims to evaluate the effect of a family involvement program (FIP) on unplanned readmissions of adult patients undergoing surgery for malignant gastrointestinal tumors. Furthermore, the study aims to evaluate the effect of the FIP on family caregiver (FC) burden and their well-being and the fidelity of the FIP.

**Methods:**

This cohort study will be conducted in 2 academic hospitals in the Netherlands. The FIP will be offered to adult patients and their FCs. Patients are scheduled for oncological gastrointestinal surgery and have an expected hospital stay of at least 5 days after surgery. FCs must be willing to participate in fundamental care activities during hospitalization and after discharge. Consenting patients and their families will choose to either participate in the FIP or be included in the usual care group. According to the power calculation, we will recruit 150 patients and families in the FIP group and 150 in the usual care group. The intervention group will receive the FIP that consists of information, shared goal setting, task-oriented training, participation in fundamental care, presence of FCs during ward rounds, and rooming-in for at least 8 hours a day. Patients in the comparison group will receive usual postoperative care. The primary outcome measure is the number of unplanned readmissions up to 30 days after surgery. Several secondary outcomes will be collected, that is, total number of complications (sensitive to fundamental care activities) at 30 and 90 days after surgery, emergency department visits, intensive care unit admissions up to 30 and 90 days after surgery, hospital length of stay, patients’ quality of life, and the amount of home care needed after discharge. FC outcomes are caregiver burden and well-being up to 90 days after participating in the FIP. To evaluate fidelity, we will check whether the FIP is executed as intended. Univariable regression and multivariable regression analyses will be conducted.

**Results:**

The first participant was enrolled in April 2019. The follow-up period of the last participant ended in May 2022. The study was funded by an unrestricted grant of the University hospital in 2018. We aim to publish the results in 2023.

**Conclusions:**

This study will provide evidence on outcomes from a FIP and will provide health care professionals practical tools for family involvement in the oncological surgical care setting.

**International Registered Report Identifier (IRRID):**

DERR1-10.2196/38028

## Introduction

### Background

Postoperative complications and hospital readmissions are known to negatively influence the short- and long-term quality of life (QoL) of patients [1]. In addition, complications and readmissions also increase health care demands and costs [2,3]. Readmission rates after gastrointestinal surgery increase up to 30% [4] and are higher compared with general surgery in that these rates range from approximately 4% to 11% [5,6]. In addition, complication rates after gastrointestinal surgery are 34% [7], which is approximately 3 to 8 times higher compared with general surgery [8,9]. Frequent complications in this patient population include delirium, pneumonia, and wound infections [7]. Reducing these readmissions and postoperative complications in patients undergoing oncological gastrointestinal surgery is a priority.

Some postoperative complications are potentially preventable [10]. Several studies have shown that optimizing basic care by executing fundamental care activities prevents postoperative complications, such as pneumonia, urinary tract infections, and delirium [10-12]. Fundamental care activities include early mobilization, breathing exercises, dental hygiene, orientation in time and place, and eating together [13]. Although fundamental care seems simple, it is prone to be missed care [13,14].

The authors of a systematic review of 18 studies concluded that up to 75% of nurses omitted some kind of fundamental care tasks [15]. In a recently published meta-review of 7 systematic reviews, the following categories of missed nursing care were identified: (1) fundamental physical care; (2) communication and information sharing with patients and families; (3) self-management, autonomy, and education of patients and families, including care planning, discharge planning, and decisions; and (4) emotional and psychological care, including spiritual support [14]. Poorly executed or missing aspects of this care threaten patients’ QoL and satisfaction, resulting in higher numbers of adverse outcomes and poor care experiences [13,14].

After hospital discharge, family caregivers often play an important role in the delivery of fundamental care activities to patients with cancer [16]. However, family caregivers often feel unprepared to deliver proper care of their loved ones after discharge, and they also feel that they lack the necessary skills and knowledge [17]. This might be because family caregivers are often considered visitors during patients’ hospital stay and are sidetracked [18]. Thus, family caregivers are not normally actively involved in postoperative care during hospitalization.

Despite the uncertainty that family caregivers experience, in the past few decades, family-centered care (FCC) has been shown to potentially improve the quality of health care [13,19-21]. Family caregivers have become important care partners who are able to participate in all aspects of care delivery [22,23]. For instance, studies in which family caregivers were actively involved in performing fundamental care activities during hospital admission have shown a reduction in postoperative complications such as delirium and pneumonia [12,24]. The authors of a review of systematic reviews concluded that FCC could be an effective approach for improving the quality of health care, but there was a lack of high-quality studies investigating the effectiveness of FCC [25].

Family caregivers might be better prepared to deliver adequate care to their loved ones after discharge if they are involved in fundamental care during hospitalization, which could also lead to improved adherence to these care activities. Therefore, the incidence of complications and related readmissions might decrease. To promote active family involvement, we developed a multicomponent family involvement program (FIP) in which family caregivers could be actively involved in caring for their loved ones during hospitalization after oncological gastrointestinal surgery [26]. In a pilot study, our FIP was shown to be feasible for patients, family caregivers, and health care professionals [16,27]. In addition, family caregivers had a better understanding and knowledge of their loved one’s recovery process [27].

### Objectives

Although the results of our pilot study on the FIP were promising, the lack of evidence on the relationship between family involvement and outcomes in patients with gastrointestinal cancer after surgery points to the need for a prospective cohort study. Therefore, the main objective of this study is to evaluate whether FIP for adult patients undergoing oncological gastrointestinal surgery reduces the number of unplanned readmissions compared with usual care. The secondary aims are to evaluate the effect of the FIP on family caregivers by assessing caregiver burden and family caregivers’ well-being and to assess the fidelity of the FIP. Here, we describe the study design and summarize the study protocol, which may also provide practical tools for health care professionals to adopt a more family-centered approach.

## Methods

### Study Design

This study is known by the acronym “ARTIS,” which stands for Activating Relatives to Get Involved in Care After Surgery. The ARTIS study is a patient preference multicenter prospective cohort study. The study protocol described here is reported according to the applicable criteria of the Standard Protocol Items: Recommendations for Interventional Trials (SPIRIT) [28] and the Template for Intervention Description and Replication (TIDieR) [29]. The results of this study will be reported according to the Strengthening the Reporting of Observational Studies (STROBE) [30].

### Study Setting

The study will be conducted at 5 surgical wards that provide care to patients after oncological gastrointestinal surgery in two Dutch tertiary university hospitals in the Netherlands: (1) Amsterdam University Medical Center (UMC), location Academic Medical Center (AMC) and Vrije Universiteit Medical Center, Amsterdam, and (2) University Medical Center Groningen (UMCG), Groningen. The average number of patients undergoing oncological gastrointestinal surgery as treatment for malignant pancreatic, gastric, esophageal, liver, colorectal, or peritoneal tumors in Amsterdam UMC is 415 per year and in UMCG 330 per year. Each participating surgical ward has 25 to 30 beds with a nursing:patient ratio of either 1:4 or 1:5. The participating wards were chosen because health care professionals expressed a willingness to adopt a more family-centered approach to their care.

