### Study Procedure

During the preoperative outpatient clinic visit, the patients and their family caregivers will be screened for eligibility and informed about the study (Table 2). If they are interested, a researcher (SM, SK, or [name]) will contact the patients after the visit to determine their preference for the study arm. If patients prefer the intervention arm, at least 2 days before hospital admission, the researcher will confirm the patients’ participation depending on the ward capacity. The FIP starts <72 hours after surgery when patients are transferred from the postanesthesia care unit to the participating surgical wards. Depending on the ward capacity and patient preferences, the program can be continued until discharge. During the follow-up period (ie, 30 and 90 days after surgery), the patient and family caregiver will be contacted by telephone by SM, SK, or [name] and asked to complete the questionnaires.

**Table 2 table2:** Study procedure.

Timing			Activity		

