### Allocation

Participation in the FIP is based on the preferences of patients and, if available, their family caregivers. This means that when the patients and their relatives want to participate in the program, they will be allocated to the intervention group and when the patients or their relatives do not want to participate in the program (but give consent for observation in the usual care group), they will be allocated to the usual care group. By using this patient preference study design, we might introduce contamination between the intervention and comparison groups, as patients in the comparison group might learn about fundamental care activities and adopt them themselves or receive informal care without the program. Nevertheless, this study design was selected deliberately because no clear signs of contamination were observed between the study groups in the pilot study [16]. To minimize the risk of between-group contamination, the information for patients and their families before inclusion will not include detailed information about the fundamental care activities that comprise the program.

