### Statistical Methods

#### Overview

Statistical analyses will be performed using the R statistical software package (version 3.6.2; R Foundation for Statistical Computing). Descriptive statistics will be used to summarize the baseline characteristics and process outcomes of the patients and family caregivers. Continuous variables will be presented as means and SDs or medians and IQRs according to the distribution of the variables. Categorical variables will be presented as counts and percentages (%), and numbers and frequencies will be presented for dichotomous data. The distribution of variables will be determined by inspecting histograms and box plots.

The patients’ baseline characteristics of the study arms will be tested for statistically significant differences using the chi-square statistics, Mann-Whitney *U* test, independent samples 2-tailed *t* test, or Fisher exact test. If there are differences between the FIP and treatment groups, we will adjust for confounding variables using multivariate regression analyses.

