#### Outcomes

Univariable regression and multivariable regression analyses will be conducted using stepwise backward selection. For the primary outcome (ie, unplanned readmissions up to 30 days after surgery), we will conduct logistic regression analyses. For continuous secondary outcomes, we will use linear regression analyses; for dichotomous outcomes, we will use logistic regression analysis. We will use a general linear mixed model to analyze differences in sleep quality, DOS scores, and AMEXO scores over 5 days after the operation (Table 1). If a difference is observed, a post hoc power analysis will be used to examine which time point differs significantly. A 2-sided *P* value ≤.05 will be considered statistically significant. A 95% CI for the beta coefficient (β) will be calculated.

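### No hospital or ward term is fixed in the primary or secondary models, so a site difference can be read as a FIP effect in this non-randomised comparison

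*Protocol article*

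**What the plan says.** All places are in the protocol article.

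- **Sites.** Study Setting: "The study will be conducted at 5 surgical wards that provide care to patients after oncological gastrointestinal surgery". There are two university hospitals, one of them with two locations. Annual volume "in Amsterdam UMC is 415 per year and in UMCG 330 per year". On staffing: "Each participating surgical ward has 25 to 30 beds with a nursing:patient ratio of either 1:4 or 1:5".
- **How groups form.** Allocation: "Participation in the FIP is based on the preferences of patients and, if available, their family caregivers". Study Procedure adds, for those who prefer the intervention, that "the researcher will confirm the patients’ participation depending on the ward capacity"; Table 2 repeats this. Sample Size sets 150 per group overall and gives no quota per hospital or ward.
- **Adjustment rule.** Statistical Methods, Overview, has baseline characteristics tested between groups, and then: "If there are differences between the FIP and treatment groups, we will adjust for confounding variables". Statistical Methods, Outcomes: "multivariable regression analyses will be conducted using stepwise backward selection".
- **Models.** The primary outcome gets logistic regression. Secondary outcomes get linear or logistic regression. A mixed model is kept for three measures repeated over five days. None is described with a hospital or ward term.
- **Baseline list.** Data Collection Methods, Patients, lists clinical, risk-screening and socioeconomic items. Tumour type, type of surgery and type of resection are there; hospital and ward are not.

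**The concern.** Nothing in the design makes the share of patients in the FIP the same at each site. Preference may differ between hospitals, and places depend on ward capacity. If readmission risk also differs between hospitals, the FIP group over-represents one hospital's risk and the usual care group the other's. The unadjusted odds ratio then mixes a hospital contrast with the FIP contrast.

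This goes beyond a detail that could wait for an analysis plan, because the article commits to a rule for choosing covariates. Following that rule can leave site out in two ways: it may never be tested, since it is not a listed characteristic, or it may be tested and then removed because its own P value is not small enough. A P value is a poor guide here. A site effect too small to be significant can still bias the FIP estimate.

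At stake is the primary result: an apparent benefit could be partly a hospital difference, or a real benefit could be masked by one. The direction cannot be told from the document.

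**Working it through.** **1. The plan's own figure.** Sample Size gives 136 per group for 35% against 20%, two-sided 5%, power 80%. With unpooled variance and no continuity correction: (1.960 + 0.842)² × (0.35×0.65 + 0.20×0.80) / 0.15² = 135.2, so 136. The pooled formula gives 138. With the continuity correction that the article names, it is 151; that mismatch is a separate matter. No site term or design effect enters. At 150 per group, power by the uncorrected pooled test is 83.2%.

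**2. Spurious difference when hospital is omitted.** Assumptions, none of them in the document: no FIP effect, two hospitals of equal size, readmission risks r₁ and r₂, FIP shares s and 1−s.

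- FIP group rate = s·r₁ + (1−s)·r₂
- Usual care rate = (1−s)·r₁ + s·r₂
- Spurious difference = usual care − FIP = (1−2s)·(r₁−r₂)

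| Risks r₁ / r₂ | FIP shares | FIP | Usual care | Spurious difference | Share of 15 points |
|---|---|---|---|---|---|
| 35% / 25% | 50/50 | 30.0% | 30.0% | 0 | 0% |
| 35% / 25% | 40/60 | 29.0% | 31.0% | 2.0 points | 13% |
| 35% / 25% | 35/65 | 28.5% | 31.5% | 3.0 points | 20% |
| 35% / 20% | 35/65 | 25.25% | 29.75% | 4.5 points | 30% |

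The table shows a false benefit. Reversing the shares gives a false harm of the same size. Weighting the hospitals 415:330 instead of equally barely changes this: 3.0 stays 3.0 and 4.5 becomes 4.4.

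**3. Effect on the test.** Same null, 150 patients per hospital, mean risk 35%, crude two-proportion z-test, nominal 5%:

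| Hospital gap | FIP shares | Spurious difference | Rejection rate |
|---|---|---|---|
| 5 points | 60/40 | 1.0 point | 5.3% |
| 10 points | 60/40 | 2.0 points | 6.4% |
| 10 points | 70/30 | 4.0 points | 11.1% |
| 10 points | 80/20 | 6.0 points | 19.2% |
| 15 points | 80/20 | 9.0 points | 37.1% |

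**4. Would the stated rule catch it?** Suppose hospital were added to the baseline tests. With 150 per group, a 60/40 imbalance would be flagged with probability about 94%, and a 55/45 imbalance with about 41%. A flagged term must then survive backward selection. The removal threshold is not stated; take P > .05 as an assumption. For risks of 35% and 25% with 150 patients per hospital, ignoring other covariates, the chance that hospital is significant is Φ[(0.10 − 1.96·√(2×0.30×0.70/150)) / √((0.35×0.65 + 0.25×0.75)/150)] = Φ(−0.07), about 47%. A 10-point hospital difference would be dropped about half the time.

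**5. Cost of adjusting.** Stratifying by hospital removes the between-hospital bias. The effective sample is multiplied by s(1−s)/0.25. Power for 35% against 20%, starting from 150 per group:

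| FIP shares | Factor | Effective n per group | Power |
|---|---|---|---|
| 50/50 | 1.00 | 150 | 83.2% |
| 60/40 | 0.96 | 144 | 81.7% |
| 70/30 | 0.84 | 126 | 76.3% |
| 80/20 | 0.64 | 96 | 64.5% |

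**The case against.** The strongest reply is that silence is not exclusion. The baseline list is not declared closed, the Overview speaks of confounding variables in general, and the Discussion calls for comparing as many prognostic variables as possible. The article condenses a fuller protocol, and a term for centre is often set elsewhere. This stands to the extent that a reader might infer that site can never be a candidate; the text does not say so. It does not remove the point, because the rule the article does state protects no covariate from removal.

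A reader might also infer that site is bound to be a confounder. The document does not support that. It needs FIP share and readmission risk both to differ by site, and neither is reported. Both groups come from the same wards, all wards were chosen because staff were willing to adopt a family-centred approach, and one tumour list covers both hospitals. Nothing shows that readmission practice differs, or that tumour type determines the ward.

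Ward capacity may look like a mechanism that moves patients between groups. Additional Analyses places patients in the group they chose before surgery, so refusal for capacity biases the contrast only if those patients are counted as usual care or lost. The article does not say which happens. Preference can still differ by site.

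It may also be tempting to say that the standard errors are invalid because of clustering. FIP status varies within wards, so this matters only as far as FIP shares differ by ward. It is secondary.

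Finally, recorded tumour and surgery variables may absorb some case-mix difference, if they survive selection. The large error rates above need very unequal shares.

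**Conclusion.** The point holds as a possibility that the plan leaves uncontrolled, not as a demonstrated bias. This is a self-selected comparison on five wards in two hospitals, with no site quota, and its stated covariate rule neither names site nor protects it. Under the assumptions shown, omitting hospital shifts the readmission difference by 2.0 to 4.5 points, or 13% to 30% of the target effect, for gaps of 10 to 15 points and shares of 40/60 to 35/65. The shift is zero when shares or risks are equal, and it grows with more extreme imbalance. No site-specific rate or FIP share is available to say where in this range the study lies.

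The change should be made. According to the Results section, follow-up of the last participant has ended, so the analysis is the remaining place to control for site.

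**What to change.** In Statistical Methods, Outcomes:

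1. Include hospital as a fixed effect in the primary and secondary models, exempt from the baseline significance screen and from backward selection.
2. Repeat the primary analysis with ward indicators in place of hospital, as a sensitivity analysis. This also separates the two Amsterdam locations if no ward spans both. With only five wards, fixed effects are more workable than a random effect.
3. Report FIP share and 30-day readmission by hospital and ward, so that readers can see whether the conditions for bias are present.
4. State how patients who preferred the FIP but were not confirmed for lack of capacity are classified.

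The cost is one parameter for hospital, or four for ward. No new data are needed for this: Data Management describes a site-specific identification log at each study site. Loss of precision is small when FIP shares are similar across hospitals (83.2% to 81.7% power at 60/40). It is real when they are very unequal (76.3% at 70/30, 64.5% at 80/20). Those are also the settings where the unadjusted estimate is most biased if hospital risks differ, so the lost power is no reason to leave hospital out.

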### Eligibility Criteria

#### Patients

In this study, we will include adult patients (≥18 years) scheduled for gastrointestinal surgery as treatment for malignant pancreatic, stomach, esophageal, liver, colorectal, or peritoneal tumors. The expected hospital stay must be at least 5 days after the operation, which makes adequate training and coaching of family caregivers under the supervision of nurses possible. Furthermore, patients will have to be able to read and write the Dutch language and will be included after providing written consent. Patients will be excluded if they remain in the intensive care unit (ICU) for >72 hours directly after surgery, as family caregivers do not have the opportunity to be involved in care in the first 5 days after the operation. In addition, patients will be excluded if the tumor is considered unresectable during surgery, as these patients do not receive the intended surgery and are discharged after one day.

